#### 2.5.2. Data Analysis

The project will use an intention-to-treat analysis. For all analyses, we will use three-level mixed-effect models, with measures nested in participants, who are themselves nested in classes/community settings. To provide a better overview of the benefits of the program, we will also use a per-protocol analysis. For all statistical analyses, we will use a two-sided α = 0.05. We will use a Bonferroni–Holm adjustment for multiple testing. When possible, the measures of effect size will be used to provide an estimation of the clinical significance of the findings. Statistical software will include Stata 15, SPSS 25, and R 3.4.3.

*Preliminary analyses:* We will examine the variables for distributional properties, correlations, and patterns of dropouts and missing data. We will compute descriptive statistics for each item and also for each scale. We will also check the reliability of the scales, especially for those that have not been described in previous studies. We will test differences between the intervention and the control group at baseline (socio-demographics and outcome variables) to confirm that the groups are comparable, especially if we cannot achieve a randomized allocation.

*H1. Increase in suicide knowledge and awareness of suicidal risks:* We will compare the mean scores of the literacy of suicide scale and the knowledge of what to do in case of suicidal thinking between the intervention and control groups.

*H2. Increase in skills related to how to seek/offer help:* We will compare the mean scores of help-seeking between the intervention and control groups.

*H2. Social networks:* Social networks of peers will be analyzed using exponential random graph models. Social networks of people outside the class are personal networks, rather than closed networks, so it will not be possible to use exponential random graph models. We will derive different variables (family support, friends’ support, other) to see whether there is an increase over time. We will explore different research questions: Is the density of social support related to suicidal thoughts and psychological distress? Is the diversity of social support related to a reduced level of suicidal thoughts and psychological distress? Does the program increase the density of social support?

*H3. Increase in skills related to the willingness and confidence to talk about suicide:* We will compare the mean scores of the willingness to talk about suicide and the confidence to talk about suicide between the intervention and control groups.

*H4. Increase in coping skills and management of adverse life events:* We will compare the mean scores of the coping subscales (and whole scale) between the intervention and control groups.

*H5. Program acceptability:* We will compute descriptive statistics of the six questions on program acceptability and of the mean score for the intervention group.

*H6. Reduction of suicidal ideation and psychological distress:* We will compare the mean scores of the suicidal ideation scale and the profile of mood states between the intervention and control groups.

In H1–H6 analyses, we will investigate the longitudinal associations (i.e., predicting the mean score at follow-up according to the group and the baseline level of the outcome variable), controlling for socio-demographic variables and other potential confounders assessed in the study. We will also consider using latent growth curve modeling.

Finally, we will compute the correlations between outcomes (knowledge, awareness, skills). Other analyses may involve subgroups for whom the intervention works better (e.g., according to socio-demographic variables, coping skills, psychological distress).

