## 2. Materials and Methods

### 2.1. Design

This study is a single-center cluster non-randomized controlled trial designed to compare an intervention group benefiting from the suicide prevention program with a control group. The study includes follow-ups at one and three months after the baseline assessment.

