### 2.2. Participants

The study will take place in different settings in the French-speaking part of Switzerland. Workshops will take place in schools (classes) and community settings (associations, vocational schools, and homes/residential centers). We will recruit clusters from these settings. All young people are eligible to participate in the study with the following exclusion criteria: (1) Being under 14 years of age and (2) not being able to communicate in French.

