### 2.3. Procedures

We will propose the study to all schools and community settings in which *Stop Suicide* delivers suicide prevention programs. We plan to rely on a random assignment to the intervention group or the control group. Participants from the control group will participate in the workshop at the end of the project. However, the final design cannot be considered as a pure randomized controlled trial since some schools or community settings may refuse to participate in the study before the workshop.

The first visit will start with the explanation of the study. Then, young people who consent to participate will complete the self-reported questionnaire (baseline assessment) (max. 20 min). 

For the intervention group, the suicide prevention program will be delivered right after to all young people, including those who did not consent to participate in the study. This one-and-a-half-hour universal program will be given in classes (or community settings) by the staff of *Stop Suicide*, who is trained to deliver it. For the control group, the first visit stops after the completion of the self-reported questionnaire.

The second visit will take place one month after the intervention (first follow-up). It will include the same questionnaires (excepted socio-demographic variables) as in the baseline assessment (max. 20 min).

The third visit will occur three months after the intervention (second follow-up). It will include the same questionnaires as in the first follow-up (max. 20 min). The control group will be delivered the workshop after the third visit.

Dissemination of information to different settings started in May 2019. Data collection will start in June 2019 and is planned to end in June 2020.

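### The model's top level is the class or setting, so classes of one school are treated as independent; whether this distorts the standard error depends on an unnamed unit of assignment

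*Protocol article*

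**What the plan says.** Section 2.5.2 (Data Analysis) fixes, for all analyses, "three-level mixed-effect models, with measures nested in participants, who are themselves nested in classes/community settings". For a community setting the setting is the top level. For a school the class is.

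Other sections place a unit above the class:

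- **2.2 Participants:** "Workshops will take place in schools (classes) and community settings (associations, vocational schools, and homes/residential centers). We will recruit clusters from these settings".
- **2.3 Procedures, approach:** "We will propose the study to all schools and community settings" that receive the programme.
- **2.3 Procedures, refusal:** "some schools or community settings may refuse to participate in the study before the workshop".
- **2.3 Procedures, assignment:** "We plan to rely on a random assignment to the intervention group or the control group". Whether schools, classes or settings are assigned is not said.
- **2.1 Design:** "This study is a single-center cluster non-randomized controlled trial".

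The models also adjust for the baseline outcome, socio-demographic variables and other confounders (2.5.2). Type of school is among the socio-demographic variables (2.4), but it is a category and does not identify the school. The article mentions no school random effect, school fixed effect or school-clustered standard error.

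**The concern.** Pupils of one school share staff, catchment and school climate, so two of its classes are likely to resemble each other more than classes of different schools do. A model that stops at the class ignores that resemblance. The consequence depends on assignment. If a whole school goes into one arm, its classes carry less independent information about the programme than the model credits, and p-values come out too small. The Holm adjustment cannot repair this, because it takes those p-values as input. If a school's classes are divided between arms, the school effect partly cancels in the comparison, and the model gives up that precision. The stake is either a false-positive risk above 5% or a loss of power.

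**Working it through.** **Plan's own figure.** Section 2.5.1 gives 95 per group for a difference of 1, variance 6, two-sided 5% and 80% power. 2 × (1.960 + 0.842)² × 6 / 1² = 94.2, rounded up to 95, or 190 in total. This reproduces, with power 0.803. It assumes independent participants and does not bear on the point here.

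**Inputs.** The documents give no intraclass correlation, no number of classes per school and no class size for the trial. Section 1 gives ten workshops a month and about 1800 young people a year: 1800 / (10 × 12) = 15 per workshop. That is a programme average; on it, 300 participants would make 300 / 15 = 20 clusters. The rest is assumed:

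- participants per class, *m* = 15
- classes per school, *c* = 1, 2 or 4
- school intraclass correlation *ρs* = 0.01, 0.02 or 0.05
- additional class correlation *ρc* = 0.03

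**Formulas** (variance relative to independent participants):

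- class-only model: *f* = 1 + (*m* − 1)(*ρs* + *ρc*)
- truth, whole schools in one arm: *t* = *f* + *m*(*c* − 1)*ρs*
- truth, classes of each school split evenly: *w* = *f* − *m ρs*
- reported SE / true SE: *r* = √(*f*/*t*) or √(*f*/*w*)
- type I error: 2 × [1 − Φ(1.96 *r*)], a large-sample approximation

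**Example**, *ρs* = 0.02: *f* = 1 + 14 × 0.05 = 1.70.

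- Two classes, same arm: *t* = 1.70 + 15 × 1 × 0.02 = 2.00; *r* = √(1.70/2.00) = 0.92; type I error 7.1%.
- Four classes, same arm: *t* = 1.70 + 15 × 3 × 0.02 = 2.60; *r* = 0.81; 11.3%.
- Even split: *w* = 1.70 − 15 × 0.02 = 1.40; *r* = √(1.70/1.40) = 1.10; 3.1%.

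**Results for *m* = 15, *ρs* from 0.01 to 0.05:**

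| Case | Reported SE / true SE | Type I error |
|---|---|---|
| One class per school | 1.00 | 5.0% |
| Two classes, same arm | 0.96 to 0.86 | 6.1% to 9.2% |
| Four classes, same arm | 0.88 to 0.70 | 8.4% to 17.2% |
| Two or four classes, split evenly | 1.05 to 1.24 | 3.9% to 1.5% |

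**Second set of assumptions**, same-arm case: school variance 0.02 to 0.05 and class variance 0.02 of a total of 1, 15 per class. With *k* classes per school, true variance = *s*s + *s*c/*k* + *s*e/(15*k*) and modelled variance = (*s*s + *s*c)/*k* + *s*e/(15*k*). For *k* = 2 and *s*s = 0.02: (0.02 + 0.01 + 0.032) / (0.02 + 0.032) = 0.062 / 0.052 = 1.19. Over the range the variance ratio is 1.19 to 1.38 for *k* = 2 (type I error 7.3% to 9.5%) and 1.58 to 2.14 for *k* = 4 (11.9% to 18.0%).

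Together, the two sets give about 6–10% with two classes per school and 8–18% with four, if schools are kept in one arm.

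**The case against.** A reader might infer that the standard errors will be too small. The documents do not support that. It needs several classes from one school, those classes in the same arm, and school variance left after adjustment, and the article establishes none of the three. Approach and refusal by school do not in themselves bias a standard error; the unit of assignment decides. If the class is the assigned cluster, the stated top level matches it, and with an even split within schools the error runs the other way. All of this stands.

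Three further limits also stand. Community settings already have the right top level, so the point touches only part of the sample. Adjustment for baseline, type of school and parental education may absorb some of the school variance, which would make the upper figures too high. Four classes per school among 20 clusters would mean only 20 / 4 = 5 schools and no community settings, an extreme case.

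A reader might also infer that large-sample z tests will be used with few clusters. The article names no test method, and that detail commonly sits in a fuller document, so this is not a fault of the plan.

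What the objection does not remove: the model is stated, for all analyses, and has no place for the school. Nothing limits a school to one class. Because a school can decline as a whole, its decision may steer how all its classes take part, which makes a shared arm plausible though not established.

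**Conclusion.** The point holds in conditional form. Where a school supplies more than one class, the stated model treats those classes as independent given the covariates. Its standard error for the programme effect is then:

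- too small if the classes share an arm and school variance remains: at 15 per class, by about 4–14% with two classes per school and 12–30% with four (first set of assumptions);
- too large, by about 5–24%, if the classes are split evenly between arms;
- unaffected if each school gives one class, because the class effect then absorbs the school effect.

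These sizes rest on assumed correlations, a class size taken from programme averages, and a single comparison without covariate adjustment in which every cluster is a school class. They illustrate direction and order of magnitude and do not forecast this trial's error rate. The model change is a cheap improvement worth making before analysis.

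**What to change.** 1. State the unit of assignment (school, class or setting), including what happens when a school declines participation before the workshop.
2. Record the identity of the school for every class. The trial already knows it.
3. Make the unit of assignment, or a higher unit, the top level of the model. Wherever a school contributes more than one class, add a school term: a random intercept above class, or school as a blocking factor if arms are split within schools.
4. As a recommendation, use Kenward–Roger or Satterthwaite degrees of freedom for the group effect in the linear models, since schools may be few (two classes per school among 20 clusters would give 10).

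The cost is one model term and a degrees-of-freedom option. Confidence intervals will be somewhat wider where classes share an arm. With few schools the school variance may be imprecisely estimated, which should be acknowledged when results are reported. No further data collection is needed.

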### 2.4. Measures

The whole French questionnaire is available in Supplementary Materials.

*Knowledge and awareness of suicide (H1)*. We will use seven items from the Literacy of Suicide Scale (LOSS) [13] to assess an increase in suicide knowledge and awareness of suicidal risks (five items of the original twelve-item scale are not discussed during the workshop). The items are assessed as true or false, leading to a total score of correct responses between 0 and 7 (Cronbach alpha = 0.77).

*Seek/offer help (H2)*. We will use the six items used in Bailey et al. [14] and a five-point scale to assess knowledge of what to do in case of suicidal risk and how to seek help. We will also use six self-developed items and a five-point scale to assess knowledge of where to seek help in the case of suicidal risk (e.g., “I know where to go for help if I have suicidal thoughts”, “I know a phone number to call for help”).

*Social network (H2)*. In addition, we will ask the participants to answer the two following questions:With which classmates do you feel comfortable speaking about problems?With which person outside the class do you feel comfortable speaking about problems?

For classmates, we will ask for first and last names in order to be able to create the complete class network. For persons outside the class, the participants will be invited to provide a first name and their relationship with this person (e.g., mother, father, sibling, friend, neighbors). We will be able to draw personal networks from this question and disentangle the family network from the peer network.

*Willingness and confidence to talk about suicide (H3)*. We will use the eight items used in Bailey et al. [14] on a five-point scale (Cronbach alphas: Willingness: 0.76, confidence: 0.60).

*Coping skills and management of adverse life events (H4)*. Two subscales from the COPE inventory [15] will be used: Seeking social support for instrumental reasons (Cronbach alpha = 0.75) and seeking social support for emotional reasons (Cronbach alpha = 0.85). Each subscale has four questions assessed on a four-point scale.

*Acceptability (H5)*. Acceptability will be assessed using six questions from Bailey et al. [14] (five-point scale).

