### 2.5. Analytical Strategy

#### 2.5.1. Sample Size Calculation

With a confidence of 95%, a power of 80%, an expected difference between the two groups of 1, and a variance of 6, a sample of *n* = 190 (95 participants in each group) is needed to detect a statistically significant difference. We plan to include *n* = 300 participants (*n* = 150 in each group).

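### The stated 80% power at 190 participants is for one unadjusted test on an unnamed outcome, but the plan tests about ten outcomes under Bonferroni–Holm with no primary

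*Protocol article*

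**What the plan says.** Section 2.5.1 (Sample Size Calculation) of the Protocol article gives one calculation: "With a confidence of 95%, a power of 80%, an expected difference between the two groups of 1, and a variance of 6". It concludes that 190 participants are required ("95 participants in each group) is needed to detect a statistically significant difference") and then sets a larger target: "We plan to include *n* = 300 participants (*n* = 150 in each group". It does not say which outcome the difference and variance belong to, why the target exceeds 190, or whether multiplicity was considered.

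Section 2.5.2 (Data Analysis) fixes the error rate ("For all statistical analyses, we will use a two-sided α = 0.05") and adds: "We will use a Bonferroni–Holm adjustment for multiple testing". The family of tests is not defined. The same section then lists the between-group comparisons hypothesis by hypothesis. H1, for example, compares "the mean scores of the literacy of suicide scale and the knowledge of what to do in case of suicidal thinking". H5 is descriptive and covers the intervention group only.

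No outcome is called primary anywhere in the article. Section 2.1 sets follow-ups at one and three months and does not give either precedence.

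**The concern.** A power statement describes one test at one significance level. Here the level in the sample-size section and the decision rule in the analysis section differ. Under Holm, the smallest p-value in a family of m tests must fall below 0.05/m before anything is declared significant. A calculation at 0.05 therefore overstates the chance of success for a given outcome, unless that outcome is tested alone or reaches the last Holm step.

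Two things are at stake. A non-significant result after adjustment could be read as failure of the program when the power was lower than stated. And because the planning difference is tied to no scale, a reader cannot judge whether a difference of 1 is plausible for any of the outcomes.

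**Working it through.** **Inputs.** From section 2.5.1: difference 1, variance 6, power 80%, confidence 95%, 95 per group needed, 150 per group planned. From section 2.5.2: two-sided 0.05 and Bonferroni–Holm.

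**Reproducing the stated figure.** Per group, n = 2 × 6 × (z for alpha + z for power)² / 1² = 12 × (1.960 + 0.842)² = 94.2, so 95 per group and 190 in total. This matches exactly. A one-sided test would give 75 per group. The stated figure is therefore one two-sided test at 0.05 with no adjustment.

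**Counting the comparisons in section 2.5.2.**

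| Hypothesis | Between-group mean comparisons | Count |
|---|---|---|
| H1 | suicide literacy; knowledge of what to do | 2 |
| H2 | help-seeking | 1 |
| H3 | willingness; confidence | 2 |
| H4 | two coping subscales; whole scale | 3 |
| H5 | none (descriptive) | 0 |
| H6 | suicidal ideation; distress or mood | 2 |
| Total | | 10 |

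The count is approximate. Leaving out the whole coping scale gives nine; the social-network measures would add to it.

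**Power at the first Holm step.** Power = Φ(√(n/12) − z), where z is the two-sided critical value. √(95/12) = 2.814 and √(150/12) = 3.536.

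| Tests in family | First-step alpha | z | 95 per group | 150 per group |
|---|---|---|---|---|
| 1 | 0.05 | 1.960 | 80% | 94% |
| 2 | 0.025 | 2.241 | 72% | 90% |
| 10 | 0.005 | 2.807 | 50% | 77% |

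With 8 or 12 tests the figures are 53% and 79%, or 48% and 75%. For 80% power at 0.005, n = 12 × (2.807 + 0.842)² = 159.8, so 160 per group and 320 in total.

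**Full Holm procedure.** Later steps use a looser alpha, so the first step is the least favourable case. A simulation (100,000 runs, ten tests, correlation between outcomes 0 to 0.5, the same standardized effect on each non-null outcome) gave this power per non-null outcome:

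| Outcomes with a true effect | 95 per group | 150 per group |
|---|---|---|
| 1 | 50% | 77% |
| 5 | 54% | 80% |
| 10 | 61–62% | 87–90% |

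Even when all ten effects are real, 95 per group does not reach 80%.

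**Clustering (assumed values).** The article gives neither an intraclass correlation (ICC) nor a cluster size. Assume 15 per cluster and a design effect of 1 + 14 × ICC. First-step power at 0.005 with 150 per group is then:
- ICC 0.01, design effect 1.14: Φ(3.536/√1.14 − 2.807) = 69%
- ICC 0.02, design effect 1.28: 62%
- ICC 0.05, design effect 1.70: 46%

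**The case against.** The strongest reply is that the trial plans 300 participants, not 190. At the strictest Holm step with ten tests that gives 77%, and 80% needs only 20 more. With about half the effects real, the full procedure already reaches 80%. Section 2.5.2 also adjusts for the baseline value of the outcome, which the calculation above ignores. If 6 is the raw variance and the baseline–follow-up correlation is r, the variance falls by the factor 1 − r². With an assumed r of 0.25, first-step power at 150 per group is Φ(3.536/√0.9375 − 2.807) = 80%; with r = 0.5 it is 90%. This stands: a reader might infer that 300 is too few because of multiplicity, and the document does not show that. It does not rescue the stated figure, since 95 per group with r = 0.5 gives Φ(2.814/√0.75 − 2.807) = 67%. Nor does section 2.5.1 link the extra participants to multiplicity; dropout and clustering would draw on the same margin.

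The family is also undefined, and an article may leave that to the full plan. If Holm runs within each hypothesis, families are smaller. Even so, two tests give 72% at 95 per group, so 80% holds only for a hypothesis with a single test. A reader might also double the family to count each follow-up separately, but the three-level models with repeated measures could yield one group test per outcome.

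Two further readings go beyond the text. One is that a variance of 6 is impossible for the literacy score. Section 2.4 describes seven true/false items, "leading to a total score of correct responses between 0 and 7 (Cronbach alpha = 0.77"). If 0.77 belongs to those seven items, KR-20 caps the variance at 1.75/(1 − 0.77 × 6/7) = 1.75/0.34 = 5.15. But the source scale has twelve items and the article does not say which version gave 0.77. For twelve items the cap is 3/(1 − 0.77 × 11/12) = 10.2, so 6 could have been borrowed from the full scale. Sum scores on other instruments could also have variance 6. The other reading is that H1 is the main effect of interest; the article ranks no hypothesis above another.

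Finally, several co-equal outcomes under Holm is a legitimate design.

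**Conclusion.** The mismatch is real and lies within the article. The 80% at 190 belongs to a single unadjusted test on an unnamed outcome, while the stated decision rule is Holm over about ten comparisons with no primary outcome or time point. Ignoring clustering, dropout and baseline adjustment, first-step power with ten tests is about 50% at 95 per group and 77% at 150; with two tests it is about 72% and 90%.

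The conclusion that 95 per group gives less than 80% does not depend on the exact count: it holds for any family of two or more at the first step. The power of the planned 300 does depend on the family, on how many effects are real, on the baseline correlation and on clustering, none of which the article specifies. The figures with clustering (69% to 46%) illustrate a range under assumed values, and omitted clustering is a separate matter. Because Holm still controls type I error and no planned test is invalid, this should be corrected but does not undermine the analysis itself.

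**What to change.** Choose one of two routes.

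1. Name one primary outcome and one time point, tested alone at two-sided 0.05, with Holm applied to the remaining outcomes as secondary. Restate the planning difference and SD on that outcome's own scale.
2. Keep the outcomes co-equal, list the tests that form the Holm family (including how the two follow-ups and the network measures enter), and restate the power of the planned 300 at the first-step alpha, 0.05 divided by the number of tests.

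Under either route, say which scale the difference of 1 and variance of 6 refer to, and what the increase from 190 to 300 is meant to cover. If clustering or baseline adjustment is brought into the restated power, give the assumed ICC, cluster size and correlation, and show a range.

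The cost is plan wording and one recalculation. Under the first route the other hypotheses become formally secondary. Neither route requires a change to data collection.

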**Hypothesis 4** **(H4).**The program increases coping skills and young people are more able to manage stress related to adverse life events.

**Hypothesis 5** **(H5).**The program is acceptable (i.e., enjoyable and worthwhile for participants).

**Hypothesis 6** **(H6).**The program reduces suicide-related behaviors (suicidal ideation) and psychological distress.

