*Suicidal ideation (H6)*. We will use two items related to the presence of suicidal ideation of the Columbia-Suicide Severity Rating Scale (C-SSRS, Cronbach alphas between 0.73 and 0.95), including a lifetime and past-month screen of suicidal thoughts (yes/no answers) [16].

*Psychological distress (H6)*. We will use the six items of the Kessler Psychological Distress Scale (K-6) [17,18] to assess psychological distress (five-point scale).

*Sociodemographic variables*. We will assess gender, age, type of school, and parental level of education.

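### H6 tests a reduction in suicidal ideation on a mean score that, as described, includes a lifetime yes/no screen and is not limited to the past month

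*Protocol article*

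**What the plan says.** - **Hypothesis (Protocol article, 1. Introduction, H6):** "The program reduces suicide-related behaviors (suicidal ideation) and psychological distress".
- **Measure (2.4. Measures):** "We will use two items related to the presence of suicidal ideation of the Columbia-Suicide Severity Rating Scale", "including a lifetime and past-month screen of suicidal thoughts (yes/no answers". No other ideation measure is described.
- **Repetition (2.3. Procedures), on the one-month visit:** "It will include the same questionnaires (excepted socio-demographic variables) as in the baseline assessment (max. 20 min". The three-month visit repeats that questionnaire. Only the socio-demographic variables are dropped, so the lifetime screen is asked again.
- **Analysis (2.5.2. Data Analysis, H6):** "We will compare the mean scores of the suicidal ideation scale and the profile of mood states between the intervention and control groups".
- **Model (2.5.2):** "For all analyses, we will use three-level mixed-effect models, with measures nested in participants". The longitudinal analysis for H1 to H6 is described as "predicting the mean score at follow-up according to the group and the baseline level of the outcome variable".

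The article does not say how the ideation answers are combined, does not limit the H6 outcome to one recall period, and does not name a model for a binary outcome.

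**The concern.** The measure and the analysis do not fit together. H6 predicts a fall. Among participants who have already had suicidal thoughts, the lifetime answer cannot truthfully fall; over one or three months it can only stay the same. Among those who have not, it can only stay the same or rise. A later no after an earlier yes would be a reporting error. A score that includes this answer therefore carries a large, nearly fixed component next to the past-month answer, which is the part that can respond.

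Two things are at stake. The first is interpretation. Section 2.5.2 intends effect sizes to convey clinical significance, and a mean of mixed recall periods does not translate into a statement about current ideation. The second is sensitivity, because the fixed component adds variance and shrinks the relative and standardised effect. Suicidal ideation is the only suicide-related behaviour that H6 names, so its outcome should be unambiguous before analysis. Leaving it open also permits a later choice between lifetime, past-month and combined scores.

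**Working it through.** **1. The article's own sample size.** Section 2.5.1 uses a difference of 1, a variance of 6, 80% power and two-sided 5%. n per group = 2 × (1.960 + 0.842)² × 6 / 1² = 94.2, rounded up to 95, so 190 in total. The figure reproduces. It does not bear on ideation: a score from 0 to 2 has variance of at most 1, and even a score from 0 to 4 (two items, each asked for both periods) has at most 4.

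**2. Assumptions.** The documents give no ideation rates. I take past-month ideation in control against intervention of 10% v 5%, 12% v 6% and 15% v 8%. Lifetime ideation L is 20%, 30% or 40% and equal in both arms. There are 150 per arm (section 2.5.1), with no clustering, no dropout and no Holm adjustment. A past-month yes implies a lifetime yes.

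**3. Dilution, before any adjustment.** Let S be the sum of the lifetime and past-month answers and p the past-month rate.
- Mean of S = L + p. The absolute difference between arms stays at p1 − p2. If the answers are averaged instead, it is halved.
- Variance of S = p(1 − p) + L(1 − L) + 2p(1 − L).

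Example with 10% v 5% and L = 30%:
- Variance of S: 0.09 + 0.21 + 0.14 = 0.440 in control; 0.0475 + 0.21 + 0.07 = 0.3275 in intervention.
- Relative reduction: past-month 0.05/0.10 = 50%; score 0.05/0.40 = 12.5%.
- Standardised difference: past-month 0.05/√(0.1375/2) = 0.19; score 0.05/√(0.7675/2) = 0.08.
- Unadjusted z: past-month 0.05/√(0.1375/150) = 1.65; score 0.05/√(0.7675/150) = 0.70.

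| Quantity, all scenarios | Past-month item | Two-answer score |
|---|---|---|
| Relative reduction | 47-50% | 10-20% |
| Standardised difference | 0.19-0.22 | 0.08-0.10 |
| Unadjusted z | 1.65-1.91 | 0.69-0.91 |

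**4. With the planned baseline adjustment.** Section 2.5.2 predicts follow-up from group and baseline level, so the unadjusted z values are not those of the planned analysis. I simulated that adjustment with a linear model: lifetime status fixed, past-month ideation in controls persisting with probability 50% or 80%, overall control rate unchanged, intervention follow-up rate multiplied by the assumed ratio, 10,000 replicates per scenario. Examples at L = 30%:

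| Control v intervention | Persistence | Power, past-month | Power, score | Loss (points) |
|---|---|---|---|---|
| 10% v 5% | 50% | 42% | 30% | 11 |
| 10% v 5% | 80% | 61% | 52% | 8 |
| 15% v 8% | 50% | 54% | 41% | 14 |
| 15% v 8% | 80% | 72% | 65% | 7 |

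Across all scenarios the loss is about 6 to 14 points. One combination (15% past-month, 20% lifetime, 50% persistence) is not attainable, because it would need an onset probability above 1; leaving it out gives 6.2 to 13.5. Power for the past-month item alone is 42% to 72%, below 80% throughout.

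**The case against.** The strongest reply is that the composite is inferred. No sentence says that the lifetime and past-month answers are added or averaged. Section 2.4 could mean two items each asked for both periods, which would allow a past-month-only score. The questionnaire is in the Supplementary Materials, which are not shown, and an article may leave scoring details to a fuller document. The sentence may also be loosely worded: it names the profile of mood states, whereas section 2.4 measures distress with the K-6 (a separate inconsistency). This tempers confidence. It does not remove the mismatch, because on either reading lifetime answers belong to the only ideation measure described, and the stated comparison does not exclude them.

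Several stronger readings are tempting and are not supported:
- **That the score discards most of the sample.** The squared ratio of the unadjusted z values (0.42-0.48) would suggest a loss of about 77-83%. That describes an unadjusted analysis. The planned baseline adjustment absorbs most of the stable lifetime component, and the power figures above correspond to a loss of roughly 13-33%.
- **That the effect is halved.** This holds for the absolute difference only if the answers are averaged, which is not stated.
- **That no programme can change lifetime ideation.** This is strictly true only for those already positive. First-ever ideation could be prevented, so a small difference is possible.
- **That a linear model is prescribed and invalid.** The article names mixed-effect models without fixing a link, so a logistic version is not excluded. For a single yes/no item a mean difference is simply the risk difference.
- **That this flaw alone would cause a false negative.** Past-month ideation by itself is underpowered here.
- **That H6 is the only hypothesis about suicide.** H1 and H3 also concern suicide; H6 is the one on ideation.

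**Conclusion.** The point holds in a limited form and should be fixed. As written, H6 tests a reduction with a mean score from yes/no screens that include a lifetime answer, and the outcome is not limited to the past month. The main damage is to interpretation: under the assumed rates, a relative reduction of 47-50% in past-month ideation appears as 10-20% on a summed score, and baseline adjustment does not turn that score into a measure of current ideation. The power loss under the planned adjustment is moderate, about 6-14 percentage points. These figures rest on assumed prevalences and persistence, 150 per arm, and no clustering, dropout or multiplicity adjustment. They also assume that the two answers are in fact combined, which the article implies but does not state.

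**What to change.** In 2.5.2 (H6), replace the comparison of mean scores of the suicidal ideation scale with wording such as: *The H6 ideation outcome is past-month suicidal ideation (yes/no) at follow-up. It will be analysed with a mixed-effects logistic model with the same clustering as the other outcomes, adjusted for past-month ideation at baseline. Lifetime ideation will be used only as a baseline covariate or descriptor. The odds ratio and the risk difference will be reported.*

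The cost is plan wording and a different link function. The logistic model may have convergence difficulty if events are sparse. No new data are needed, since the past-month screen is already collected at every visit. The change makes the result interpretable and recovers the moderate power loss, but it does not make the ideation comparison adequately powered at 150 per arm in the scenarios examined.
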